### Medical record review

The medical record review will be conducted by experienced clinical auditors trained in assessing adherence to evidence-based diabetes management guidelines. Data will be systematically recorded using a customized Excel spreadsheet developed specifically for this study, containing all predefined audit criteria.

The review will focus on newly diagnosed type 2 diabetes mellitus (T2DM) patients, particularly those with an HbA1c value ≥6%, to assess whether appropriate clinical services and interventions were delivered in line with guideline recommendations.

The collected data will allow a comprehensive evaluation of healthcare provider adherence, identifying gaps in clinical care and informing quality improvement initiatives across PHCC settings. *(see*
Table 1
*for data collection variables).*

**Table 1 pone.0313664.t001:** Clinical Audit Criteria and Variables.

Criterion	Description
Criterion 1	ASCVD risk assessment for all adult patients (≥40 years) at diagnosis
Criterion 2.1	Laboratory Investigations: HbA1c, lipid profile (TC, HDL, LDL, TG), serum creatinine and eGFR, liver function (ALT, AST), urine albumin/creatinine ratio, TSH (if dyslipidemia or female >50 years), urine ketones (if glucose >250 mg/dL), serum potassium (if on ACEi/ARB/diuretics)
Criterion 2.2	Initial general foot examination
Criterion 2.3	Referral to eye specialist for initial retinal assessment
Criterion 3	Documentation of HbA1c target goals
Criterion 4	Appropriate treatment initiated or adjusted based on guidelines
Criterion 5	Patient education on diet and physical activity at initial visit
Criterion 6	Referral to dietitian for Medical Nutrition Therapy (MNT)
Criterion 7	Follow-up HbA1c test ordered within 3–6 months from treatment initiation

Source: PHCC clinical practice guideline for the management of Type 2 Diabetes.

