## Abstract

Type 2 Diabetes Mellitus (T2DM) remains a global health challenge, with increasing prevalence in the Middle East, especially in Qatar. The Primary Health Care Corporation (PHCC) is the main provider of diabetes care in the country. Systematic evaluation through clinical audits provides a structured approach to identify gaps and improve clinical practices. This study aims to evaluate the effectiveness of clinical audit-based interventions in enhancing the management and documentation of T2DM in PHCC settings in Qatar. This quasi-experimental study will be conducted in three phases: pre-intervention, intervention, and post-intervention. In the pre-intervention phase, a cross-sectional situational analysis will be conducted across 31 PHCC health centers by reviewing 450 randomly selected patient records of adults diagnosed with T2DM. A baseline analysis will identify gaps in adherence to evidence-based diabetes care guidelines. The intervention phase will introduce specific quality enhancement strategies, which will encompass staff training, the distribution of guidelines, the engagement of audit champions, and various additional initiatives. Post-intervention, another 450 records will be audited to assess improvement. Additionally, 60 patients will be surveyed via telephone before and after the intervention to assess perceptions of care. The ICAE-DM CARE study aims to evaluate enhancements in clinical documentation, evaluation, and assessment of co-morbidities among patients with diabetes, alongside screening practices, adherence to evidence-based management protocols, and patient satisfaction levels. The findings will facilitate the institutionalization of audit-driven quality improvement initiatives within primary care settings. By providing robust evidence for integrating clinical audits into routine diabetes management, the study seeks to improve patient outcomes and support the objectives outlined in Qatar’s National Health Strategy.

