### Study population

The study population includes adult patients (≥ 18 years) who are non-pregnant and have attended PHCCs for the management of type 2 diabetes within the past two years. Patients can be newly diagnosed or on follow-up.

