### Sample selection

A stratified simple random sampling method will be employed to select representative samples for both the cross-sectional and cohort components of the study. For the cross-sectional analysis, a total of 450 patient records will be randomly selected from the medical records department across 31 health centers. This sample size was calculated based on a 5% margin of error, a 95% confidence interval, and an assumed response distribution of 50%, with an additional allowance for potential non-responses. The selection will take place at two different time points: baseline and post-intervention, with 450 cases reviewed at each stage to facilitate a comparative analysis of diabetes-related encounters over the preceding three months.

For the patient satisfaction component, a subset of 60 patients will be randomly selected at each time baseline and post-intervention—from the larger cohort. These patients will be contacted by telephone to complete satisfaction surveys, offering qualitative insights into their perceptions of care. The randomization process will be independently applied at both time points to ensure comparability and minimize selection bias. A sample size of 60 patients per time point is considered sufficient to balance feasibility with the need for meaningful analysis of patient satisfaction trends. This approach ensures the robustness and reliability of findings and supports a comprehensive evaluation of both clinical outcomes and patient perspectives throughout the intervention period.

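### The record audit samples new and follow-up patients, but its review text targets new diagnoses and up to five of nine audit lines concern events around diagnosis or treatment start, so those lines have no defined denominator

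*Protocol article*

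**What the plan says.** The sampled population is broad. The Abstract describes "450 randomly selected patient records of adults diagnosed with T2DM". Study population adds: "Patients can be newly diagnosed or on follow-up". The Inclusion Criteria ask for a documented diagnosis and two or more visits in two years. They set no limit on diagnosis date and no HbA1c value. Sample selection states that "a total of 450 patient records will be randomly selected from the medical records department across 31 health centers", at baseline and again after the intervention, to support "a comparative analysis of diabetes-related encounters over the preceding three months". It calls the sampling stratified but names no stratum for diagnosis status.

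Medical record review narrows this: "The review will focus on newly diagnosed type 2 diabetes mellitus (T2DM) patients, particularly those with an HbA1c value ≥6" per cent. Table 1 follows directly. Its lines include "ASCVD risk assessment for all adult patients (≥40 years) at diagnosis" (Criterion 1), "Initial general foot examination" (2.2), a first retinal referral (2.3) and "Patient education on diet and physical activity at initial visit" (5). Criterion 7 is timed from the start of treatment. Lines 2.1, 3, 4 and 6 have no such tie, and Criterion 4 expressly covers adjustment of treatment as well as its initiation.

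**The concern.** The words chosen to narrow the review do not say whether a follow-up record that is drawn is left out, scored, or marked not applicable on the diagnosis and first-visit lines. The answer sets the denominator of those lines in both waves.

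The intervention lasts 8–9 months, while eligibility looks back two years for visits and without limit for diagnosis. A patient diagnosed before the intervention was therefore diagnosed at least 8–9 months before the second audit, outside its three-month window. On the lines tied to diagnosis or first visit, such a record either carries a score for care given before the intervention or drops out. In the first case the before–after difference is diluted. In the second, fewer records are assessable than the sample size was built on.

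The HbA1c wording adds a smaller, conditional point. If the value is used to pick records, each picked record must already hold an HbA1c result, and HbA1c testing is one component of Criterion 2.1.

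**Working it through.** **Inputs from the article.** 450 records per wave; margin of 5 points, 95% confidence and assumed proportion of 50% (Sample selection); significance at 0.05 (Analytical plan). **Not given:** the share *s* of newly diagnosed patients among the 450, so a range is shown. A two-sided test is assumed.

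**The plan's own figure.** n = z²p(1−p)/d² = 1.96² × 0.25 / 0.05² = 384.1, so 385. Reaching 450 implies a non-response allowance of 1 − 385/450 = 14.4%. The article mentions an allowance without giving its size, so 450 is consistent with the inputs but not fixed by them. The planned ±5 needs 385 assessable records, which is 385/450 = 85.6% of the sample.

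**Table 1 lines.**
- Tied to diagnosis or first visit/assessment: 1, 2.2, 2.3, 5 (four of nine).
- Timed from treatment initiation: 7 (making five of nine).
- No such tie: 2.1, 3, 4, 6.

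**Two alternative scenarios for the tied lines.**

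(a) Only new patients are scored. Half-width = 1.96 × √(0.25/(450s)).

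(b) All 450 are scored and records of earlier-diagnosed patients cannot change. Half-width = 1.96 × √(0.25/450) = ±4.6 whatever *s* is, but the observed gain is *s* × the true gain.

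| Assumed share s | New records | (a) margin, points | (b) observed gain if true gain is 10 points |
|---|---|---|---|
| 100% | 450 | ±4.6 | 10 |
| 75% | 337.5 | ±5.3 | 7.5 |
| 50% | 225 | ±6.5 | 5 |
| 25% | 112.5 | ±9.2 | 2.5 |
| 10% | 45 | ±14.6 | 1 |

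**Power, as illustration.** Assume a true rise from 50% to 60% in new patients, none in the others, and equal waves.

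| s | (a) only new scored | (b) all scored |
|---|---|---|
| 100% | 86% | 86% |
| 75% | 74% | 62% |
| 50% | 57% | 32% |
| 25% | 33% | 11% |
| 10% | 16% | 5% |

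Under (b), 80% power would need 388 records per wave at s = 100%, 693 at 75% and 1,565 at 50%.

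**The case against.** The best defence is that a focus within a broad population is loose drafting and not a second eligibility rule. Study population covers the whole study, including the telephone survey, and stratum or extraction detail may sit in a fuller protocol. That weakens any claim of two strict definitions. It does not settle the denominator: the sampling text sets no filter on diagnosis date, and the review text does not say what happens to a follow-up record once drawn.

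Other objections stand and limit the point:

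- A reader might infer that follow-up records cannot show any effect. Table 1 does not support that. They remain informative on lines 2.1, 3, 4 and 6. A follow-up patient who never had a foot examination or retinal referral could arguably still have a first one during the intervention (2.2, 2.3). Criteria 1 and 5 are the clearly fixed ones.
- A reader might infer that most of the audit is affected. That holds only at five of nine lines, counting Criterion 7; on strict wording it is four.
- A reader might add the wider margin to the diluted effect. They are alternatives: if only new patients are scored, nothing is diluted; if all are scored, the margin does not widen.
- A low share of new patients should not be presumed. The stated focus on new diagnoses points towards higher shares, so the range must include no loss at all.
- A change in the mix of new and follow-up patients between waves could mimic an effect. However, the article specifies random selection and the same methodology both times, and gives no reason to expect a shift.
- The HbA1c wording is not stated as a selection rule. If used as one, it would fix one component of a multi-test criterion, equally in both waves.

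**Conclusion.** The concern holds in limited form and should be fixed. The sampling text and the review text do not describe one population, and for four of nine audit lines, five with Criterion 7, the denominator depends on which is followed.

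The size cannot be fixed from the article because the share of new patients is not given. If at least 85.6% of the 450 are new, the planned ±5 is kept on these lines with only new patients scored. At an assumed 50% the cost is a margin of ±6.5 or, alternatively, half of the true gain. At 10% it is ±14.6 or nine-tenths of the gain. Scenario (b) rests on the assumption that tied items in earlier-diagnosed patients cannot change. That is firm for Criteria 1 and 5 and less so for 2.2 and 2.3.

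The article does not support the conclusion that the audit as a whole cannot detect improvement, or that the HbA1c value will be used to select records. The clinical cut-off itself is not judged here.

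**What to change.** Reconcile the Abstract, Study population, Inclusion Criteria and Sample selection with Medical record review, and state one sampling frame, used in both waves and defined by recorded diagnosis date.

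- For lines 1, 2.2, 2.3, 5 and 7, make the denominator patients diagnosed in an index window. At the second wave it must start after implementation. In both waves it must be the same length and allow Criterion 7 to be observed; a window covering only the preceding three months would leave many patients short of the 3–6 months that criterion refers to.
- If follow-up patients are kept, sample them as a separate stratum, score them only on the lines that apply, and report them separately.
- Do not select records on the HbA1c value, or reconcile it with the Inclusion Criteria. A record selected that way meets the HbA1c component of Criterion 2.1 by construction.

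**Cost.** Protocol wording and a record query on diagnosis date; the target of 450 per wave can stay if supply allows. Conclusions on the diagnosis and first-visit lines would apply to newly diagnosed patients only. The article does not give the number of new diagnoses available per window, so it must be checked first. If it is below 385, restate the margin for these lines. Timing is tight: if the second audit comes 8–9 months after implementation and each patient needs the full six months from a treatment start close to diagnosis, only diagnoses in the first 2–3 months (8 − 6 to 9 − 6) qualify for Criterion 7.

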### Analytical plan

Data will be extracted from the electronic health record system at two separate points: one time at a point before the intervention and the other time at a point after the implementation of the intervention. Excel will be used to collect and organize the data. PivotTables will be used to determine the frequency of cases across variables. Excel will be further used to produce histograms and other figures.

Study outcome variables will be assessed using independent tests like Chi square or t test to compare between the two groups. For satisfaction, we will do it frequently by percentage P=(F/T) *100.

The statistical analysis will be performed using STATA 15.1 (College Station, TX, USA). A Wilcoxon sign rank test will be used to find the mean difference between the pre- and post-assessment. P < 0.05 will be considered statistically significant. A logical model of protocol presented in Fig 2.

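### The protocol does not settle whether the 450 records per round come from newly diagnosed or all type 2 diabetes patients, so audit items fixed at diagnosis or first visit can score pre-intervention care in round 2

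*Protocol article*

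**What the plan says.** The Study population section admits adults who attended for type 2 diabetes within two years and adds: "Patients can be newly diagnosed or on follow-up". The inclusion criteria ask for two encounters in that period and set no diagnosis date. Sample selection then draws records at random across the 31 centers, "with 450 cases reviewed at each stage to facilitate a comparative analysis of diabetes-related encounters over the preceding three months". The three months qualify the encounters, not the diagnosis.

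The Medical record review section describes a narrower group: "The review will focus on newly diagnosed type 2 diabetes mellitus (T2DM) patients". It gives no time limit for newly diagnosed and does not make it a condition of the draw.

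Some items in Table 1 are tied to the start of care. Criterion 1 reads "ASCVD risk assessment for all adult patients (≥40 years) at diagnosis". Criterion 5 concerns education at the first visit. Criteria 2.2 and 2.3 concern a first foot examination and a referral for a first retinal assessment, without a date. Criterion 7 is a repeat HbA1c order timed at 3–6 months from the start of treatment.

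Under Intervention and follow-up, the action plan runs for 8–9 months, and round 2 then repeats the round-1 method.

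**The concern.** The before-after contrast is the study's only evidence of effect. On an item fixed at diagnosis or first visit, a round-2 patient diagnosed before the action plan contributes a pre-intervention observation. If such patients are in the round-2 sample, the contrast mixes care given under the intervention with care given before it, and the estimated change shrinks towards zero.

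The affected items are not marginal. Evaluation of audit impact names risk assessment documentation, referrals and patient education among the key outcome indicators. It also says that minimal improvement will lead to refinement of the implementation strategy, so a diluted result could be misread as poor implementation.

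A second risk arises if auditors resolve the conflict by keeping only the newly diagnosed among the 450 already drawn. The sample for these items then falls, and the stated precision may not be met.

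**Working it through.** **1. The plan's own figure.** Sample selection states: "This sample size was calculated based on a 5% margin of error, a 95% confidence interval, and an assumed response distribution of 50" per cent, "with an additional allowance for potential non-responses".

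- n = 1.96² × 0.5 × 0.5 / 0.05² = 384.1, rounded up to 385.
- The allowance has no figure. Going from 385 to 450 implies 1 − 385/450 = 14.4%.
- With all 450 records the margin is 1.96 × √(0.25/450) = 4.6 points.

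The 450 is reproduced.

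**2. Which items are exposed to the problem, for a round-2 patient diagnosed before the start.**

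| Criterion | Effect |
|---|---|
| 1 (at diagnosis), 5 (first visit) | The scored event lies before the intervention and cannot change |
| 2.2, 2.3 (first foot examination, first eye referral) | Affected only if the event had already taken place; a missing one can still occur during the intervention |
| 7 (repeat HbA1c order) | Affected only if its 3–6 month window had already passed |
| 3, 4, 6 | Not tied to diagnosis or first visit as worded |

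**3. Dilution on an item fixed at diagnosis or first visit.** Let f be the share of round-2 patients diagnosed after the start. If the others still show the baseline rate, observed change = f × true change.

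The protocol does not give f. As an illustration, assume diagnoses spread evenly over the 24-month look-back and round 2 directly after the 8–9 month phase. Then f = 8/24 to 9/24 = 33% to 38%. Assume also a true rise from 50% to 65%.

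Power is for a simple two-sample comparison, ignoring clustering by center, with 450 per round. The protocol sets "P < 0.05 will be considered statistically significant"; a two-sided test is assumed. With p̄ the mean of the two proportions and d their difference:

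power ≈ Φ{[d − 1.96√(2p̄(1−p̄)/450)] / √[(p₁(1−p₁)+p₂(1−p₂))/450]}

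For d = 0.05: (0.05 − 1.96 × 0.03329)/0.03325 = −0.459, so power is 0.323.

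| f | Observed change (points) | Power |
|---|---|---|
| 100% | 15.0 | 99.6% |
| 75% | 11.25 | 93% |
| 50% | 7.5 | 62% |
| 37.5% | 5.6 | 39% |
| 33.3% | 5.0 | 32% |
| 12.5% | 1.9 | 8% |

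The first row is the no-harm case. It applies if newly diagnosed means within 8 months or less of a round 2 held straight after the intervention. The low rows apply if many long-standing patients are drawn, as the eligibility text allows.

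**4. Margin if the newly diagnosed are selected after the draw.** Margin = 1.96 × √(0.25/n), for an item scored in every retained record.

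| Records kept | Share of 450 | Margin (points) |
|---|---|---|
| 385 | 86% | 5.0 |
| 338 | 75% | 5.3 |
| 225 | 50% | 6.5 |
| 135 | 30% | 8.4 |
| 45 | 10% | 14.6 |

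The 5% margin holds down to 385 records and fails below that. The shares are assumptions.

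**The case against.** The strongest reply is that the sections can be read together. Eligibility may be a general statement that also serves the telephone survey, while the 450 cases are newly diagnosed patients whose diagnosis falls in the three months before each audit. After an 8–9 month intervention every round-2 patient would then be exposed, with n still 450. The text does not exclude this, but it does not say it: the three months refer to encounters, and follow-up patients are expressly admitted. A three-month diagnosis window would also sit badly with Criterion 7. The reading shows that harm is not inevitable; it does not remove the need to reconcile the sections.

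A reader might infer that all the initial-care items are locked in the past. The document does not support that. Criteria 2.2 and 2.3 carry no date, and the section on audit champions lists foot-examination documentation and referral adherence among the changes made.

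A reader might also infer that the study must lose either its contrast or its margin. That does not follow either. Drawing 450 from recently diagnosed patients at the outset would keep both.

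Finally, an article may leave the operational definition of newly diagnosed to the full protocol or audit tool. That is fair for the missing definition alone. It does not answer the conflict between two stated audit populations, or the bias that follows if the sampling is carried out as written.

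**Conclusion.** The conflict is real and should be resolved before records are drawn. Study population, the inclusion criteria and Sample selection describe one audit population; Medical record review describes another. Followed as written, the sampling biases the before-after change towards no change: firmly for Criteria 1 and 5, and conditionally for 2.2, 2.3 and 7. The bias is roughly in proportion to the share of round-2 patients diagnosed before the start.

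That share is unknown. The range runs from no dilution to a change of about one third of its true size at 33% to 38% exposed, and smaller still if long-standing patients dominate. The power figures rest on an assumed rise from 50% to 65%, evenly spread diagnoses and simple random samples. They illustrate the mechanism and do not predict this study's power. Loss of the 5% margin is an alternative consequence, and arises only if the restriction is applied after the draw and leaves fewer than 385 records.

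**What to change.** Reconcile Study population, the inclusion criteria, Sample selection and Medical record review on who is audited. In each round, define the record-audit frame as patients whose first recorded type 2 diabetes diagnosis falls in a calendar window of fixed, equal length. The round-1 window closes before the action plan starts; the round-2 window opens after it starts. Draw the 450 from that frame.

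Alternatively, keep follow-up patients but stratify the draw by diagnosis date, score the diagnosis and initial-visit items only in the newly diagnosed stratum, and state the margin for that stratum.

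Under either option, score Criterion 7 only in patients with enough follow-up for its 3–6 month window and state its smaller denominator. If six full months are required and round 2 follows directly, only diagnoses in the first 8 − 6 = 2 to 9 − 6 = 3 months of the intervention qualify, taking treatment to start at diagnosis.

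The cost is a wording change and a diagnosis-date filter on the record query. There are two downsides. Conclusions on these items apply only to newly diagnosed patients. And enough new diagnoses must exist in each window, which the protocol does not show; if they do not, the margin must be restated for the number available.
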